### Standard supportive care protocol

All participants will receive standardized oral care per MASCC/ISOO guidelines [17]. This supportive regimen, implemented uniformly across both study arms, includes professional oral hygiene protocols, weekly dental assessments, supervised use of non-alcoholic mouthwashes, and systematic lip hydration.

Upon clinical diagnosis of ulcerative OM, localized therapeutic PBMT (660 nm, 2 J/spot, 100 mW, 20s, 20.41 J/cm²) will be initiated until complete repair [30]. When a preventive application point coincides with an ulcerated region, therapeutic irradiation will replace the preventive dose at that point. Total therapeutic sessions and cumulative energy will be recorded as potential confounders.

Procedures follow safety standards and manufacturer recommendations, including wavelength-specific protective eyewear for patients and operators. To prevent cross-contamination, handpieces will be disinfected with 70% isopropyl alcohol and covered with disposable PVC film.

Although PBMT is low-risk, participants will be monitored for adverse effects, (e.g., transient discomfort, thermal sensation, or erythema). Any event will be documented, and therapy will be discontinued if reported or observed.

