### Intraoral PBMT

IO PBMT will be administered using the Therapy EC device (DMC^®^, São Carlos, SP, Brazil). This system utilizes an Aluminum Gallium Indium Phosphide (AlGaInP) semiconductor diode laser featuring a single-emitter laser (0.098 cm²). The procedure will be performed in contact mode using a visible red wavelength of 660 nm.

The device operates at an output power of 100 mW, resulting in an irradiance of 1.02 W/cm². Each application point will receive 1 J of energy over a 10-second irradiation interval, corresponding to a fluence of 10.20 J/cm² (Table 1).

Application Technique: A 44-point protocol covers the buccal mucosa [29]. The anatomical distribution is defined as follows:

Buccal mucosa: 16 points (8/ side).Labial mucosa: 8 points (4 superior and 4 inferior).Buccal folds: 6 points (3/ side).Tongue: 9 points (4 on each lateral border and 1 on the tip).Soft palate: 3 points.Labial commissures: 2 points (1/ side).

Total energy is 44 J/ session, lasting 440 s (7 min and 20 s). The clinical mapping of these points is illustrated in Fig. 3.

Three calibrated examiners will perform all clinical assessments; however, blinding will not be feasible in this study due to the visually distinguishable nature of the two PBMT protocols.

For both TC and IO protocols, PBMT will not be applied directly to the gross tumor volume (GTV), as defined in the IMRT planning records available in the patient’s medical record. In cases where any predetermined application point coincides with the GTV, the point will be repositioned or omitted, and this decision will be recorded on the data collection form.

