### Statistical analysis

Analyses will be performed using Jamovi software (version 2.6.44). Normality will be assessed using the Shapiro-Wilk test, and variables will be described using frequencies and percentages (categorical variables) or means, standard deviations, and medians with interquartile ranges (continuous variables). Baseline comparability between groups will be assessed using Student’s t-test or the Mann-Whitney U test (continuous variables) and the chi-square test or Fisher’s exact test (categorical variables).

The primary outcome, oral mucositis severity (WHO scale), will be analyzed longitudinally using a mixed-effects ordinal logistic regression model to account for the repeated measurements. The model will include treatment group, assessment time, and the treatment vs. time interaction as fixed effects, with participant included as a random effect to account for within-subject correlation. Total radiotherapy dose, tumor location, and concomitant chemotherapy will be included as covariates.

Pain intensity (NRS) will be analyzed longitudinally using an appropriate mixed-effects regression model according to its distribution. The primary analysis will follow the intention-to-treat principle. Missing outcome data will not be imputed; instead, the mixed-effects ordinal logistic regression model will incorporate all available repeated measurements and account for incomplete observations over time under the assumption that data are missing at random.

The primary objective is to determine whether transcutaneous infrared PBMT is non-inferior to intraoral red PBMT regarding oral mucositis severity. Non-inferiority will be assessed using the estimated treatment effect obtained from the longitudinal mixed-effects model and interpreted according to the prespecified non-inferiority margin of 0.5 WHO grade.

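### Ulcers trigger 660 nm PBMT with the intraoral laser's parameters in either arm, so the primary WHO-grade model compares preventive route plus shared rescue and cannot alone support a claim about prevention

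*Protocol article*

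**What the plan says.** **Rescue.** Under Standard supportive care protocol: "Upon clinical diagnosis of ulcerative OM, localized therapeutic PBMT (660 nm, 2 J/spot, 100 mW", for 20 s, "20.41 J/cm²) will be initiated until complete repair". Where an ulcer coincides with a preventive point, "therapeutic irradiation will replace the preventive dose at that point". The rule names no arm and stands in the section on care given to all participants. The phrase "implemented uniformly across both study arms" describes the hygiene, mouthwash and lip-care regimen. That rescue also applies to both arms is inferred from its placement and from the absence of any restriction.

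**Devices.** The Intraoral PBMT section describes a laser "featuring a single-emitter laser (0.098 cm²") and "using a visible red wavelength of 660 nm", at 100 mW. The Transcutaneous PBMT section uses only the 808 nm emitters, with spots of 0.029 and 0.233 cm².

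**Endpoint and analysis.** Table 2 makes WHO grade 2 the first ulcerative grade, and grading takes place at each visit. Under Statistical analysis, "the mixed-effects ordinal logistic regression model will incorporate all available repeated measurements", following intention to treat. The covariates are radiotherapy dose, tumor location and chemotherapy. The per-protocol set depends only on completing 80% of PBMT sessions.

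**Handling of rescue.** "Total therapeutic sessions and cumulative energy will be recorded as potential confounders".

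**Claim.** The Introduction's primary objective and the Expected results both concern prevention of OM.

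**The concern.** The trial asks whether TC prevents oral mucositis as well as IO. Once a TC participant ulcerates, however, the ulcerated sites are treated with the comparator's wavelength, power, spot size and irradiance. The Introduction itself says that PBMT speeds healing of established lesions and shortens severe mucositis, so on the protocol's own reasoning rescue lowers later grades. The arm with more ulcers receives more rescue.

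If TC is the weaker preventive, part of its deficit is repaired before the model sees it. In a superiority trial this would be conservative. In a non-inferiority trial it works in favour of the claim. A true TC deficit is a live possibility: the TC sections concede that the soft palate is not covered and that fluence at the mucosa is 10 to 50 times lower than at the skin.

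Calling rescue a potential confounder does not help. Rescue occurs after randomisation and is caused by the outcome, so adjusting for it would condition on a consequence of treatment.

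**Working it through.** **1. Whose laser is the rescue laser?** Fluence = energy / spot area.

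- Reproducing the stated fluence with the IO spot: 2 J / 0.098 cm² = 20.41 J/cm², as stated. Solved backwards: 2 / 20.41 = 0.0980 cm².
- Irradiance: 20.41 J/cm² / 20 s = 1.02 W/cm², the IO value in Table 1. The TC emitters run at 3.45 and 0.43 W/cm².
- Energy per point: 2 J, against 1 J in IO prevention.

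**2. Which grades are affected?** Grades up to and including the visit at which the first ulcer is diagnosed precede rescue. Participants who never ulcerate are unaffected. What remains is grades recorded under rescue, or influenced by it, after a first ulcer. The Introduction puts OM of any grade at 75% to 90% in this population. It gives no frequency for ulcerative OM, so the share of visits affected is unknown.

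**3. Illustration of size.** From the document: margin 0.5, one-sided α 0.025, power 80%, 27 per arm, 10% attrition. Assumed:

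- 24 evaluable per arm (27 × 0.9 = 24.3).
- SD. None is stated. The value at which 24 per arm gives 80% power is 0.5 × √(24/2) / (1.960 + 0.842) = 0.618.
- f, the share of visits after rescue, and r, the share of the TC deficit that rescue removes at those visits. Neither has a source in the document.

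SE = 0.618 × √(2/24) = 0.178. Observed difference = 0.5 × (1 − f·r). P(non-inferiority) = Φ((0.5 − observed)/SE − 1.96). This is a normal approximation on mean grades, not the planned ordinal model.

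| f | r | Observed difference | False non-inferiority, SD 0.618 | Same, SD 1.0 |
|---|---|---|---|---|
| 0 | – | 0.50 | 2.5% | 2.5% |
| 0.3 | 0.25 | 0.46 | 4.0% | 3.4% |
| 0.5 | 0.50 | 0.375 | 10.4% | 6.3% |
| 0.7 | 0.75 | 0.24 | 31% | 14.7% |

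With the noncentral t, the SD 0.618 column becomes 4.0%, 10.1% and 30.2%.

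**4. Does the shrinkage survive when both arms get the same rescue?** The formula in step 3 assumes that rescue narrows the gap, so this was checked with a small simulation of grade transitions. All its settings are assumed: 20 visits; chance of worsening per visit 0.22 in IO and 1.5 times that in TC; chance of improving 0.08. At grade 2 or more, rescue multiplies worsening by 0.6 and improvement by 2.

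| Rescue | TC mean grade | IO mean grade | Difference |
|---|---|---|---|
| None | 2.33 | 1.68 | 0.66 |
| Equal effect in both arms | 1.85 | 1.33 | 0.52 |
| Mainly effective in TC (IO multipliers 0.9 and 1.2) | 1.85 | 1.59 | 0.26 |

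Both rescue scenarios move the difference towards zero. By how much depends on whether rescue adds more in TC than in IO, where the participant is already receiving 660 nm.

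**The case against.** The strongest reply is that the protocol can be read as a treatment-policy comparison. Study Design and Setting says the aim is to compare each protocol's overall clinical performance. The section on clinical and treatment-related variables calls the design pragmatic, although it does so when explaining why chemotherapy patients are included. The primary analysis is intention to treat on all data. On that reading, grades after rescue are the outcome and not contamination. This stands: the primary analysis is legitimate for that question. It does not settle the matter, because the stated objective and hypothesis are about prevention.

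Three further points also stand.

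- A reader might infer that every WHO grade after the first ulcer is the comparator's doing. Rescue is localized and ends at repair, so only grades under or influenced by it are affected.
- A reader might infer that the protocol adjusts for rescue. It only records it, and the primary covariate list omits it. The fault is the label, which invites a harmful adjustment later.
- The error rates rest on an assumed SD, f and r, and on a simpler test than the planned one. With equal rescue in the simulation, the difference stayed above the margin (0.52).

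Supplementary analyses and rules for events after randomisation may also be in an SAP that is not shown. That is why the point rests on what the article states: a prevention claim, a primary analysis that includes rescued grades, and the confounder label.

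**Conclusion.** The concern holds in a conditional form. The match between rescue and the IO laser is exact. If TC prevention is truly worse and rescue is effective, the primary comparison moves towards non-inferiority. If the arms do not differ and rescue works equally, there is little or no distortion. It would therefore be wrong to conclude that the primary analysis is biased in all circumstances, or invalid.

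The size cannot be computed from the documents. Under the assumptions above (true deficit 0.5, SD 0.62, 24 per arm), false non-inferiority is about 4% to 30% against a nominal 2.5%. With SD 1.0 it is about 3% to 15%. These figures illustrate direction and are not properties of this trial.

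The practical conclusion is that a non-inferior result would apply to preventive route plus common 660 nm ulcer care. Taken alone, it could not be attributed to TC prevention.

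**What to change.** Leave the rescue rule unchanged and amend the analysis text.

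1. State that the primary non-inferiority result refers to the preventive route together with the common 660 nm rescue.
2. Add a key supportive analysis by arm of time to, and cumulative incidence of, first WHO grade 2 or more. That event precedes rescue and can be derived from the grades already recorded at each visit. Word any claim about prevention in the light of it. The 0.5-grade margin does not carry over to this endpoint, so report the estimate with its confidence interval.
3. Replace the confounder label: therapeutic sessions and cumulative energy are to be reported by arm as post-randomisation outcomes and not entered as covariates in the treatment comparison.

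Carrying the worst grade forward after rescue is a tempting alternative, but it should not be made a condition for claiming non-inferiority. It is not free of rescue, because the higher grades that rescue averted are never seen. It also discards real healing, and the 0.5 margin was not set for such a score.

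Cost: a few sentences and one extra analysis, with no new data. With 54 participants that analysis will be imprecise, and the prevention claim becomes more limited if the two results disagree.

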## Randomization and blinding

Participants will be randomized (1:1) to TC or IO groups via Random.org (*n* = 54). The research team will perform sequential, simple randomization without blocks or stratification. Due to the distinct application methods and wavelengths (red vs. infrared), double-blinding is unfeasible. Moreover, outcome assessors responsible for WHO and NCI-CTCAE oral mucositis grading cannot be blinded, as the clinical team involved in treatment delivery will also perform the evaluations. Therefore, this is an open-label trial, and the lack of blinding represents a potential limitation of the study. To minimize potential detection bias, examiners will undergo calibration before study initiation, standardized assessment criteria will be applied, and photographic documentation will support mucositis evaluation.

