## Clinical and treatment-related variables

Prophylactic PBMT will be administered thrice weekly during radiation therapy. Following institutional standards, all patients will undergo intensity-modulated radiation therapy (IMRT). The prescribed radiation regimen consists of total doses ranging from 60 to 70 Gy, delivered in 30 to 35 fractions of 2 Gy (200 cGy) per fraction, five days a week.

Following a pragmatic design, patients on concurrent chemotherapy will be included. As chemotherapy significantly impacts OM risk, it will be recorded and treated as a covariate in multivariable regression analyses to adjust for potential confounding on outcomes.

The standardized PBMT schedule was set for Monday, Wednesday, and Friday during all weeks of RT, ensuring a maximum interval of two days between sessions and coverage of at least three consecutive RT fractions. Three times per week (rather than daily) was based on the operational feasibility of the referral oncology service (patient flow and researcher availability), evidence from randomized clinical trials demonstrating that the efficacy of three-times-weekly PBMT protocols is comparable to daily frequency in SCC populations [22], and protocols approved by the MASCC/ISOO guidelines that include alternate frequencies [17].

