### Data collection

All study data, including research-specific instruments and clinical forms, will be stored in both physical file folders and on a password-protected personal computer under the direct responsibility of the principal investigators. To ensure confidentiality, participants will be de-identified using unique numerical codes.

At baseline, a Case Report Form (CRF) will record demographics (age, sex), oncological diagnosis, and comorbidities. During each PBMT session, participants will undergo systematic clinical evaluation. Any clinical changes, adverse reactions, or OM progression will be documented on a standardized longitudinal follow-up form to monitor the incidence and trajectory of oral lesions throughout treatment.

The primary clinical endpoint:

OM severity

Will be assessed by a trained examiner at each clinical visit. To ensure a comprehensive evaluation of both functional and clinical aspects, severity will be graded according to the established criteria of the World Health Organization (WHO) and the National Cancer Institute Common Terminology Criteria for Adverse Events (NCI-CTCAE) [31] (Table 2).

The WHO scale will be used to integrate objective clinical signs (erythema and ulceration) with the patient’s functional ability to maintain oral intake. Simultaneously, the NCI-CTCAE scale will provide a standardized grading of symptomatic and clinical toxicity. The detailed scoring criteria for both instruments are summarized in Table 2.

**Table 2 Tab2:** Classification of OM according to the WHO and NCI scales

Scales	WHO	NCI
0	Normal mucosa	Normal mucosa
1	Erythema	Erythema
2	Ulcer, normal diet	Non-contiguous ulcers up to 1.5 cm in diameter
3	Ulcer, liquid diet	Contiguous ulcers larger than 1.5 cm in diameter
4	Ulcer, unable to tolerate oral intake	Ulcers with necrosis and bleeding

2.)Topographic mapping of oral lesions

To accurately track the progression and resolution of OM, a systematic topographic mapping of the oral cavity will be performed during each clinical evaluation. The presence, extension, and anatomical location of erythema and ulcerative lesions will be documented using a standardized oral cavity map.

The assessment will encompass the following anatomical sites:

Non-keratinized mucosa: Buccal mucosa, labial mucosa, ventral/ lateral tongue, soft palate, and floor of the mouth.Keratinized mucosa: Dorsum of tongue and hard palate.

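### The adverse-event rule, read literally, ends randomized PBMT for trivial effects and does not say whether the application, the session or the course stops

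*Protocol article*

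**What the plan says.** The rule is in the protocol article under Standard supportive care protocol. After calling PBMT low-risk, it says "participants will be monitored for adverse effects, (e.g., transient discomfort, thermal sensation, or erythema"), and then "Any event will be documented, and therapy will be discontinued if reported or observed". The sentence applies to both arms. It gives no severity grade, no attribution criterion and no restart rule.

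The same section keeps treating once mucositis ulcerates. Localized therapeutic PBMT "will be initiated until complete repair", and "When a preventive application point coincides with an ulcerated region, therapeutic irradiation will replace the preventive dose at that point".

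Under Treatment adherence and discontinuation, PBMT discontinuation means at least two consecutive missed sessions, or stopping the intervention altogether. These participants are not excluded. They are analysed by ITT with the data gathered until they withdraw. A per-protocol sensitivity analysis keeps only those with 80% or more of their scheduled sessions.

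Under Data collection, "The WHO scale will be used to integrate objective clinical signs (erythema and ulceration") together with oral intake, and Table 2 makes erythema grade 1 on both the WHO and the NCI scale. Severity "Will be assessed by a trained examiner at each clinical visit". Under Randomization and blinding, "the clinical team involved in treatment delivery will also perform the evaluations".

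**The concern.** This is a printed operating rule, not a detail left to another document, and its own examples are minor and short-lived. The only place where the article says what discontinuing PBMT means is the adherence section, and that meaning is more than a pause at one point. Put together, a passing sensation of warmth can end the randomized intervention.

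In a non-inferiority comparison this matters in two ways. Patients who stop early receive less of what they were assigned, so the ITT contrast describes a weaker version of one or both protocols. The same patients then fall below the 80% threshold, so the per-protocol analysis meant to check the ITT result loses them. The choice among the possible readings is left to unblinded staff who also grade the primary outcome.

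A second, smaller difficulty is the word erythema. It names a possible PBMT effect and is also grade 1 mucositis, and the article gives no rule for telling the two apart on mucosa.

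**Working it through.** **Inputs.** "Prophylactic PBMT will be administered thrice weekly during radiation therapy", with 30 to 35 fractions given five per week (Clinical and treatment-related variables). Energy is 44 J per session in 44 points of 1 J for the intraoral (IO) arm, and 32 J per session in eight applications of 4 J for the transcutaneous (TC) arm (Table 1). The per-protocol threshold is 80% of scheduled sessions. I assume no radiotherapy breaks and a Monday start. The article gives no adverse-event rate, so there is no figure of its own to reproduce.

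**Scheduled sessions.** 30 / 5 = 6 weeks × 3 = 18. 35 / 5 = 7 weeks × 3 = 21.

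**Per-protocol threshold.** 0.80 × 18 = 14.4, so 15 sessions are needed and 3 may be lost (15/18 = 83.3%). 0.80 × 21 = 16.8, so 17 are needed and 4 may be lost (17/21 = 81.0%). Session 15 is the Friday of week 5. Session 17 is the Wednesday of week 6.

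**Loss from one event, by reading.**

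| What stops | Loss | Per-protocol set |
|---|---|---|
| One application, IO | 1/44 = 2.3% of a session; 1/(44 × 18) = 0.13% to 1/(44 × 21) = 0.11% of course energy | stays in |
| One application, TC | 4/32 = 12.5% of a session; 4/(32 × 18) = 0.69% to 4/(32 × 21) = 0.60% of course energy | stays in |
| One session | 1/18 = 5.6% to 1/21 = 4.8% of sessions | stays in |
| Two consecutive sessions | 2/18 = 11.1% to 2/21 = 9.5% of sessions | stays in (16/18 = 88.9%; 19/21 = 90.5%) |
| Course, after week 2 | only 6/18 = 33.3% or 6/21 = 28.6% delivered | out |
| Course, after week 3 | only 9/18 = 50.0% or 9/21 = 42.9% delivered | out |

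Weeks 2 and 3 are illustrative. The Discussion dates the appearance of PBMT benefit to that period; it does not say that adverse effects occur then.

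**How many patients, if one event ends the course.** Suppose an independent chance p of any minor event at each session. This is an assumption, not a value in the article. The share who stop at some point is 1 − (1 − p)^s, with s = 18 or 21. The share who drop out of the per-protocol set is 1 − (1 − p)^14 or 1 − (1 − p)^16, counting the session in which the event occurs as completed.

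| Assumed p | Stopped at any time (18; 21 sessions) | Below 80% (18; 21 sessions) |
|---|---|---|
| 1% | 16.5%; 19.0% | 13.1%; 14.9% |
| 2% | 30.5%; 34.6% | 24.6%; 27.6% |
| 5% | 60.3%; 65.9% | 51.2%; 56.0% |
| 10% | 85.0%; 89.1% | 77.1%; 81.5% |

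With 27 patients per arm, p = 1% would remove about 0.131 × 27 = 3.5 to 0.149 × 27 = 4.0 per arm from the per-protocol set. Under the course reading even a rare minor effect would therefore count.

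**Consistency of the text.** If erythema in the stopping rule included mucositis, redness would stop PBMT while an ulcer would call for more of it, at 2 J instead of 1 J per spot. Data collection also lists adverse reactions and mucositis progression as separate items on the follow-up form. Both points show that the authors did not mean a stop for grade 1. Neither tells the operator how to classify redness seen on the mucosa.

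**The case against.** The strongest reply has four parts.

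- **The wording is loose, but the intent is clear.** The events are introduced as adverse effects of a low-risk device, so a relation to PBMT is implied. That stands: what is missing is a stated attribution criterion, not the idea of relatedness.
- **Severity grades and stopping levels usually sit in a full protocol or safety manual.** That is fair for an omission. Here, though, the article prints an unconditional rule with trivial examples, and a fuller document would have to contradict it to repair it.
- **The harm arises only under the course reading.** True. An application or session stop matters little, and even a two-session gap leaves the patient in the per-protocol set. The text does not choose among these readings, and its only definition of discontinuation points away from the mildest ones.
- **The analysis already copes.** Patients who stop PBMT remain in the study and in ITT, adherence is recorded, and per-protocol is only a sensitivity analysis. This rules out a claim that patients are excluded. It does not restore the treatment they did not receive.

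A reader might infer that the rule stops treatment for grade 1 mucositis, and that this falls on the IO arm because its contact surface is mucosa. The article does not support either step. It never states a stop for grade 1, it treats through ulcers, it separates adverse reactions from mucositis progression, and the stopping sentence and the grading apply to both arms. What remains is an ambiguity about mucosal erythema.

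**Conclusion.** The point holds as a defect of wording with possible consequences for treatment delivery. As printed, trivial PBMT effects can end randomized treatment, and the stopping level is left open. The effect is negligible if an application stops, about 5% of the course if a session stops, and large if the course stops before session 15 of 18 or session 17 of 21. These figures assume 18 to 21 sessions without radiotherapy breaks.

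The number of patients affected is unknown because no event rate is given; the shares calculated from assumed rates only show sensitivity. The direction by arm is also unknown. The Discussion allows that intraoral treatment may be uncomfortable for patients in severe pain, which would weaken the comparator, but thermal sensation or skin erythema could lead to stops in the TC arm. A reader might infer a bias towards non-inferiority, and the article does not establish one. It is worth correcting, with medium confidence, because the change is cheap.

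**What to change.** Under Standard supportive care protocol, replace the stopping sentence with a rule to this effect:

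- Every event is documented with its site, its attribution and the action taken.
- Transient discomfort, thermal sensation or erythema attributed to PBMT interrupts only the current application or session, and the next scheduled session goes ahead.
- Only a persistent or clinically significant event attributed to PBMT, on skin or mucosa, ends the course. One definition applies in both arms, and reasons are recorded and reported by arm.
- Erythema or ulceration attributed to mucositis is outcome data and does not by itself stop PBMT. The words about attribution are needed: a blanket ban on stopping for mucosal erythema would also prevent stopping for a true laser reaction.

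Under Treatment adherence and discontinuation, state that WHO grades obtained at the planned clinical visits after a PBMT stop enter the ITT analysis, for example by grading at the weekly dental assessments.

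The cost is wording in two sections and a case report form field for the reason for each stop. There are three small downsides. Attribution still rests on unblinded staff. The sponsor must define persistent or clinically significant. The sponsor must also confirm that the weekly dental assessments include WHO grading, since the article describes them only as supportive care; if they do, no extra visits are needed.
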